### **10.2 Secondary and exploratory study parameters**

Adverse events will be compared by tabulating all grade 3 and 4 adverse events for each patient and calculating the proportion of in each group. The incidence of complications will be compared between groups with the chi-square test or Fishers exact test.

In the exploratory analyses, we will assess differences by comparing mean values between the groups using either a two-tailed student's t-test or non-parametric equivalents, paired if pre-treatment values are compared with post-treatment values, unpaired if comparisons are made between groups. For discrete variables (e.g. the number of positive assays), the chi-squared test or Fisher's exact test will be used (two-tailed).

As an exploratory analysis data will also be visualized on an individual patient level to evaluate the progression or correction of vitamin K deficiency in relationship to other parameters associated with COVID-19 disease severity.

### **10.3 Interim analysis**

There will be no interim data analysis. Fifty percent of the study patients, 10 intervention and 10 controls, has insufficient power to conduct a classical interim analysis to evaluate either the primary or secondary endpoints. Instead, the SMC will conduct a safety analysis that will focus on identifying any serious negative effect of the study intervention on patient safety.

The SMC will have access to the unblinded patient data for all serious adverse events and thromboembolisms that occurred during the trial. If a significantly higher number of SAEs or thromboembolisms occurred in the intervention group compared to the control group, the SMC will advise the sponsor to place the study on hold pending a more extensive review. In the case of such a safety hold, the trial will only be restarted after discussion with the METC that assessed the study.

## **11. ETHICAL CONSIDERATIONS**

### **11.1 Regulation statement**

This study will be conducted according to the principles of the Declaration of Helsinki (Brazil 2013, [www.wma.net](http://www.wma.net)) and in accordance with the Medical Research Involving Human Subjects Act (WMO), GCP and the GDPR.

The investigator will be thoroughly familiar with the appropriate use of the study drug as described in the protocol and Investigator's Brochure. Essential clinical documents will be maintained to demonstrate the validity of the study and the integrity of the data collected. The Sponsor's Trial Master File (TMF) will be maintained at the sponsor site (CWZ). Each participating site will maintain an investigator site file (ISF). This study file will be established at the beginning of the study.

The ethics committee(s) will review all appropriate study documentation in order to safeguard the rights, safety and well-being of the patients. The study will only be conducted at sites where ethics approval has been obtained. The investigator will provide the relevant ethics committee(s) with the final version of the protocol, patient information and consent forms, any other written information given to patients, safety updates, annual progress reports, and any revisions to the study protocol or any other trial documentation

### **Protocol compliance**

The investigator will conduct the study in compliance with the protocol given approval/favorable opinion by the ethics committee(s), the appropriate Regulatory Authority(ies) and, if required, institutional department(s) such as Research & Development Department. Changes to the protocol will require approval from the sponsor and written ethics committee approval/favorable opinion prior to implementation, except when the modification is needed to eliminate an immediate hazard(s) to patients. The ethics committee(s) may provide, if applicable Regulatory Authority(ies) permit, expedited review and approval/favorable opinion for minor change(s) in ongoing studies that have the approval /favorable opinion of the ethics committee(s). The investigator will submit all protocol modifications (non- compliance) to the regulatory authority(ies) in accordance with the governing regulations. Any deviations from the protocol must be fully documented in the source documents.

### **11.2 Recruitment and consent**

The method of obtaining and documenting the informed consent and the contents of the consent will comply with ICH-GCP and all applicable regulatory requirement(s):

Patients will be informed about the study by their treating physician. After initial information, patients will be given the informed consent form and additional information about the study can be provided by the study nurse or researcher.

A properly signed and personally dated informed consent form is required for each patient before any trial specific procedure. After the study has been fully explained the patient should be given ample time to read the consent forms and ask questions.

Written informed consent will always be obtained from the patient prior to study participation. The informed consent process should be recorded in source documents (date of information and consent, parties present).

The investigator is responsible for checking entries made by the patient on the consent form, and to request correction immediately in case of missing, illegible or incorrect dates. The person taking the patient consent should sign and date both consent forms to confirm he/she provided information to the subject.

The Informed Consent form will be updated by the investigator whenever important new information becomes available that may be relevant to subject's consent. This may be a result of amendments to the protocol, new information regarding the trial medication alternative treatments. Revised versions must be approved by the relevant ethics committee(s).

The revised consent form must be signed by subjects who are entered in the trial and not yet completed, if these changes are relevant to the subject's willingness to continue participation. In particular, if the consent form is updated with new safety information, a new version of the informed consent form must be provided to all subjects still participating in the trial in a timely manner as soon as written ethics approval is obtained. Patient withdrawal of consent from the study should be explicitly documented in the source documents.

After the patient signs informed consent the study physician will also inform their primary contact person designated in their patient file.

### **11.3 Benefits and risks assessment, group relatedness**

This is a double blind therapeutic randomized safety clinical trial. Half of the patients will receive the intervention which may be beneficial for the trial subject. There is a potential benefit for participants in this study if vitamin K2 is shown to help prevent complications from COVID-19. However, there is no preliminary causal evidence for this relationship.

Risks for participants are related to three interventions: 1) taking vitamin K2 MK-7, 2) repeated blood draws, 3) extra low-density CT scan(s). To date no adverse side-effects from

vitamin K2 MK-7 supplementation have been described in persons who do not use vitamin K antagonists (VKAs). Blood will be drawn by venapuncture or through an intravenous cannula at regular time points as part of routine patient care. In study participants 25ml extra blood will be three times a week during admission. This volume is not expected to have consequences for the health of the patients.

Finally, in participants one or two extra low dose CTs will be made outside routine care for COVID-19. The risks of this are expected to be minimal as the radiation exposure of a single low-dose CT is low.

#### **11.4 Compensation for injury**

The sponsor/investigator has a liability insurance which is in accordance with article 7 of the WMO.

The sponsor (also) has an insurance which is in accordance with the legal requirements in the Netherlands (Article 7 WMO). This insurance provides cover for damage to research subjects through injury or death caused by the study.

The insurance applies to the unexpected damage that becomes apparent during the study or within 4 years after the end of the study.

## **12. ADMINISTRATIVE ASPECTS, MONITORING AND PUBLICATION**

### **12.1 Handling and storage of data and documents**

Data and documents will be controlled and processed conform the EU General Data Protection Regulation (GDPR) and the Dutch Act on Implementation of the General Data Protection Regulatio. (in Dutch: Uitvoeringswet AVG, UAVG).

In order to maintain patient privacy, all data capture records, study drug accountability records, study reports and communications will identify the patient by the assigned patient number. The full patient name should never be used in any correspondence the case report forms.

### **12.2 Case Report Forms**

Data will be collected on electronic Case Report Forms (CRF) to document eligibility, safety and efficacy parameters, compliance to treatment schedules and parameters necessary to evaluate the study endpoints. Data collected on the CRF are derived from the protocol and will include at least:

- Inclusion and exclusion criteria
- Baseline status of patient including medical history and stage of disease;
- Timing and dosage of protocol treatment;
- Baseline concomitant diseases and adverse events;
- Parameters for response evaluation;
- Any other parameters necessary to evaluate the study endpoints;
- Survival status of patient;

The e-CRF will be completed on site by the local investigator or sub-investigator or an authorized staff member. The CRF must be signed by the local investigator or sub-investigator upon completion by means of an electronic signature. All CRF entries must be based on source documents.

### **12.3 Subject confidentiality**

Each patient is assigned a unique patient study number at enrolment. In trial documents the patient's identity is coded by patient study number as assigned at enrolment. The local investigator will keep a subject enrolment and identification log that contains the key to the code, i.e. a record of the personal identification data linked to each patient study number. This record is filed at the investigational site and should only be accessed by the investigator and the supporting hospital staff, and by representatives of the sponsor or a regulatory agency for the purpose of monitoring visits or audits and inspections.

Only encoded data may be shared with other study groups for research purposes.

#### **12.4 Filing of essential documents**

It is the responsibility of the principal investigator at the study center to keep all essential documents relating to the trial for at least 15 years after the completion or premature termination of the clinical trial. Essential Documents are those documents that permit evaluation of the conduct of a trial and the quality of the data produced and show whether the institution complied with the principles and guidelines of good clinical practice. The essential documents may be subject to, and should be available for, audit by the sponsor's auditor and inspection by the regulatory authority(ies).

The investigator should file all essential documents relevant to the conduct of the trial on site. The sponsor will file all essential documents relevant to the overall conduct of the trial. Essential documents should be filed in such a manner that they are protected from accidental loss and can be easily retrieved for review. The archived data can be kept in electronic form, provided the protocol, ethical and government approvals, together with all other documents concerning the study, including any audit and inspection certificates are all to be kept as part of the trial master reference file. All data about serious adverse events and occurred thromboembolisms also need to be kept in this trial master file.

The medical files of patients enrolled into the trial must be kept in accordance with national legislation and for the maximum period of time permitted by the institution.

#### **12.5 Storage of samples**

Storage of biological samples on site is subject to the site's guidelines; samples may be labeled with the patients identifying information (e.g. name, hospital record number). Samples that are shipped to another facility for a purpose as described in this protocol or for additional scientific research, should be stripped from any identifying information and labeled with a the trial name and individual patient's study code.

#### **12.6 Monitoring and Quality Assurance**

Before study initiation, the protocol and eCRFs together with relevant SOPs will be reviewed by the sponsor, the investigators and their staff. During and after completion of the study, the data monitor will visit each site to check the completeness of records, the accuracy of entries on the eCRFs, the adherence to the protocol and to Good Clinical Practice, the progress of enrolment, and to ensure that Vitamin K2 and placebo are being dispensed and accounted for according to protocol.

The site will maintain source documents for each subject in the study consistent with hospital guidelines, including admission and visit notes containing demographic and medical

information, laboratory data, and the results of any other tests or assessments. Data concerning the primary outcome is drawn from these source documents and recorded in the eCRFs. The investigator will also keep the original informed consent form signed by the subject (a signed copy is given to the subject).

The investigator will give the data monitor access to all relevant source documents to confirm their consistency with the eCRF entries. Though there are no indications of possible adverse effects from Vitamin K2 MK-7 supplementation, this study has been classified as 'middle risk' according to the NFU risk classification system based on the vulnerability of the study population. The monitor will perform full verification for the presence of informed consent, adherence to the inclusion/exclusion criteria and documentation of SAEs. The recording of data that will be used for all primary and safety variables will be assessed for 10% of included subject (i.e. 4 subjects).

### **12.7 Amendments**

Amendments are changes made to the research after a favourable opinion by the accredited METC has been given. All amendments will be notified to the METC that gave a favourable opinion. A 'substantial amendment' is defined as an amendment to the terms of the METC application, or to the protocol or any other supporting documentation, that is likely to affect to a significant degree:

- the safety or physical or mental integrity of the subjects of the trial;
- the scientific value of the trial;
- the conduct or management of the trial; or
- the quality or safety of any intervention used in the trial.

All substantial amendments will be notified to the METC and to the competent authority. Non-substantial amendments will not be notified to the accredited METC and the competent authority, but will be recorded and filed by the sponsor.

### **12.8 Annual progress report**

The sponsor will submit a summary of the progress of the trial to the accredited METC once a year. Information will be provided on the date of inclusion of the first subject, numbers of subjects included and numbers of subjects that have completed the trial, serious adverse events/ serious adverse reactions, other problems, and amendments.

**12.9 Temporary halt and (prematurely) end of study report**

The sponsor will notify the accredited METC and the competent authority of the end of the study within a period of 90 days. The end of the study is defined as the last day of follow-up for the last patient (defined as discontinuation of treatment).

In case the study is ended prematurely, the sponsor will notify the accredited METC within 15 days, including the reasons for the premature termination.

Within one year after the end of the study, the investigator/sponsor will submit a final study report with the results of the study, including any publications/abstracts of the study, to the accredited METC.

**12.10 Public disclosure and publication policy**

This trial will be registered in [clinicaltrials.gov](https://clinicaltrials.gov) prior to study start. The final report will be prepared by the investigators at the Canisius Wilhelmina Hospital. It will be signed by the project leader and on behalf of the sponsor. The investigators will make every effort to publish the results in a peer-reviewed journal.

## 13. STRUCTURED RISK ANALYSIS

### 13.1 Potential issues of concern

#### a. Level of knowledge about mechanism of action

Vitamin K2 in the form of menaquinone-7 is approved as a nutritional supplement in the European Union and is readily available in stores in The Netherlands.

The activity of vitamin K in general, including Vitamin K2 MK-7 specifically, has been studied both *in vitro* and *in vivo*. Its role as a cofactor for the enzyme  $\gamma$ -glutamate carboxylase (GGCX) during the reaction in which it carboxylates glutamate residues into  $\gamma$ -carboxyglutamate (Gla) has been described extensively [28]. Vitamin K has been extensively studied for its critical role in activating hepatic coagulation factors II, VII, IX and X, protecting against bleeding disorders that are seen in patients with a severe deficiency [59]. The mechanisms by which vitamin K contributes to bone health by acting as a cofactor for the carboxylation of osteocalcin has also been explored in many human studies [49].

Vitamin K is crucial for the activation of MGP via the same mechanism of vitamin-K-dependent carboxylation by GGCX. The importance of MGP to preventing vascular calcifications has been highlighted by many cohort studies associating increased levels of dp-ucMGP (uncarboxylated MGP) with increased vascular calcifications. There are also multiple studies showing that vitamin K supplementation has a favorable effect on vascular calcification, though large scale studies are still ongoing [25, 51]. It has been hypothesized that vitamin K protects pulmonary elastic fibers through a similar mechanism, but this remains to be definitively established [23].

Less is known about the role of vitamin K in anticoagulation pathways. Through the same mechanism as procoagulation factors, vitamin K is required for the carboxylation of anticoagulant protein C and protein S [60, 61]. It has been theorized that an initial vitamin K insufficiency would result in deficient activation of endothelial protein S before causing a decrease in carboxylated prothrombin. This would explain the seemingly paradoxical increase of thrombosis risk in the first week of treatment with VKAs [18, 62].

#### b. Previous exposure of human beings with the test product(s) and/or products with a similar biological mechanism

Vitamin K2 in the form of menaquinone-7 is approved as a nutritional supplement in the European Union and is readily available in stores in The Netherlands.

Pharmacokinetics of vitamin K2 MK-7 have been previously examined in humans [25, 46, 47]. Studies both in healthy volunteers and hemodialysis patients have used dosages of vitamin K2 MK-7 similar to the dosage in this trial without any safety concerns, including thrombotic complications [46, 47, 49-51].

c. Can the primary or secondary mechanism be induced in animals and/or in ex-vivo human cell material?

In a previous study we have used available biobanks of plasma from COVID-19 patients to establish much of the correlations between vitamin K status, MGP, elastic fiber degradation and clinical outcome.

Though SARS-CoV-2 can infect other species, robust animal disease models of COVID-19 are lacking. *Ex-vivo* human cell cultures can and have been used to study the activity of vitamin K on a molecular basis, but these cannot capture the complexities of pharmacokinetics and tissue distribution that will be studied in this clinical trial.

d. Selectivity of the mechanism to target tissue in animals and/or human beings

The activity of vitamin K is not tissue specific. The triage theory posits that in times of vitamin K insufficiency it is first used to activate intrahepatic coagulation proteins at the cost of extrahepatic proteins like osteocalcin, MGP and endothelial protein S [3, 26, 62]. We have previously demonstrated that COVID-19 patients with extrahepatic vitamin K deficiency shown by elevated levels of dp-ucMGP, had normal levels of activated hepatic coagulation protein factor II [26]. As there are no indications that additional vitamin K supplementation in persons with fully activated hepatic coagulation proteins leads to a prothrombotic state, vitamin K supplementation in COVID-19 patients will likely selectively affect carboxylation of extrahepatic proteins.

The function of vitamin K is conserved between different species and toxicity studies in animal models have shown no adverse effects of high doses [27].

e. Analysis of potential effect

The safety and tolerability of vitamin K2 MK-7 supplementation in COVID-19 patients will be extensively assessed in this study. Supplementation will only be provided during hospital admission, where patients will be seen by a physician daily, and complete laboratory assessment will be performed three times a week.

The effects of vitamin K on carboxylation status of both hepatic and extrahepatic proteins will be assessed by measuring PIVKA-II and dp-ucMGP, respectively.

f. Pharmacokinetic considerations

Vitamin K2 MK-7 has a longer half-life than most other forms of vitamin K, which has been extensively studied in healthy humans. Unlike other fat-soluble vitamins, both animal toxicity studies and observations from neonates administered high doses of vitamin K as prophylaxis

have shown no evidence of accumulation of vitamin K in tissues or formation of toxic metabolites.

#### g. Study population

Patients with COVID-19 requiring supplemental oxygen will be included in the study. Patients who are already admitted to the Intensive Care will not be included, however, admission to the ICU during the study does not require discontinuation of treatment. As additional protection against thrombotic complications all patients will be administered either prophylactic or therapeutic dosages of heparin-like anticoagulants. Pregnant women will not be included into the study.

#### h. Interaction with other products

The only known interaction risk with vitamin K are vitamin K antagonist drugs. Patients may not use VKAs during the study. If a patient is using VKAs at admission and wishes to participate in the study they must be switched to therapeutic dosages of heparin-based anticoagulants. In this case vitamin K2 MK-7/placebo treatment may only be initiated after the patient has received at least one dose of heparin-based anticoagulant.

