### 3. STUDY DESIGN

This is a double-blind, placebo-controlled randomized phase 2a intervention study in male and female patients over 18 years old with COVID-19 requiring supplemental oxygen and hospital admission. Patients will be treated with oral vitamin K2 or placebo from day 1 until discharge, with an expected average hospital stay duration of 6 days. After written informed consent is obtained from the patients or a legal representative, eligible patients will be randomized between the intervention (vitamin K2, in the form of menioquinone-7) and control (placebo) groups.

Patients randomized to the intervention group will take three tablets of vitamin K2 menaquinone-7 333mcg per day (for a total dose of 999mcg per day), from day 1 until day 14 or discharge, whichever occurs first, figure 3. Patients in the control group will receive a matched placebo. Adverse events will be collected daily and blood will be sampled three times a week until discontinuation of treatment. A low-dose chest CT scan will be made at admission and 5 days after treatment. If a patient is discharged before day 5 post treatment, a CT scan will be made before discharge. Mortality and serious adverse events will be followed up on day 28.

Patients will receive all routine treatment for COVID-19 according to general hospital practice.

[figure not shown]

**Figure 3:** Clinical trial design.

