#### **8.3.3 Follow-up of adverse events**

Adverse events will be monitored until discontinuation of treatment, at 28 days post inclusion mortality will be assessed.

When recording adverse events special attention will be paid to progression of respiratory insufficiency, thrombotic events, pulmonary embolism or deep venous thrombosis and bleeding. Toxicities will be scored according to the most recent version of the NCI Common Terminology Criteria for Adverse Events (CTCAE) version 5 (see Appendix).

The treating physician will determine whether adverse events require additional testing, such as, for example, pulmonary CT angiography in the case of suspected pulmonary embolism or coagulation parameters in the case of bleeding.

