### 8.3.12 Study flow chart

|                                                                      | Inclusion      | Hospital admission |                    | Follow-up |
|----------------------------------------------------------------------|----------------|--------------------|--------------------|-----------|
| Study day                                                            | 1              | 2-14   | 15-27  | 28        |
| Eligibility criteria + informed consent                              | X              |                    |                    |           |
| Collection of demographic data and medical history                   | X              |                    |                    |           |
| Physical examination and vital signs                     | X              | X                  | X                  |           |
| Vitamin K2 MK-7 or placebo treatment                                 | X              | X                  |                    |           |
| Collecting (serious) adverse events                                  |                | as necessary       |                    |           |
| Collecting adverse events                                            |                | X                  |                    | X         |
| Laboratory testing                                     | X  | X                  | X                  |           |
| dp-ucMGP, PIVKA-II, desmosine                          | X  | X                  | X                  |           |
| Plasma and serum collection for exploratory endpoints  | X  | X                  | X                  |           |
| CT scan                                                              | X  | X      |                    |           |

 Vital signs are collected at least 3 times per day until discharge, physical examination is performed as necessary

 Blood is collected three times per week while the patient is admitted to the hospital

 Full blood count, electrolytes (sodium, potassium, calcium), creatinine, liver enzymes (bilirubin, ALAT, ASAT and LDH), c-reactive protein (CRP) and albumin; d-dimer will be determined at all follow-up time points (though not at baseline)

 Analysis performed retrospectively

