### 9.2.2 Serious adverse events (SAEs)

A serious adverse event is any untoward medical occurrence or effect that:

- results in death;
- is life threatening (at the time of the event);
- requires hospitalisation or prolongation of existing inpatients' hospitalisation;
- results in persistent or significant disability or incapacity;
- is a congenital anomaly or birth defect; or
- any other important medical event that did not result in any of the outcomes listed above due to medical or surgical intervention but could have been based upon appropriate judgement by the investigator.

An elective hospital admission or outpatient visit will not be considered as a serious adverse event.

The investigator will report all SAEs to the sponsor without undue delay after obtaining knowledge of the events.

As symptoms in COVID-19 patients are often progressive after admission, an adverse event that prolongs hospitalization will only be considered a serious adverse events if, according to the investigator, it falls outside the natural progression of COVID-19.

Serious Adverse Events (SAEs) will be reported from the first study-related procedure until discharge from the hospital (at which time treatment will be discontinued) or until study day 28 if the patient is still admitted at that time. SAEs will be followed up for every patient on study day 28.

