#### **9.4.3 Follow-up of (serious) adverse events**

All adverse events will be followed clinically until they have been resolved, or until a stable situation has been reached. Depending on the event, follow up may require additional tests or medical procedures as indicated, and/or referral to the general physician or a medical specialist.

SAEs need to be reported till end of study within the Netherlands, as defined in the protocol as treatment discontinuation for the last patient.

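### The protocol sets conflicting windows for recording safety events, so whether a post-discharge SAE or thromboembolism reaches the safety committee's between-arm comparison depends on the section followed and on length of stay

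*Protocol*

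**What the plan says.** Six places in the protocol bear on when safety events stop being collected.

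- **Section 3:** "Mortality and serious adverse events will be followed up on day 28".
- **Section 8.3.3:** "Adverse events will be monitored until discontinuation of treatment, at 28 days post inclusion mortality will be assessed". Section 9.2.1 likewise limits grade 3 and 4 adverse events in the eCRF to those that start or worsen between first treatment and treatment discontinuation.
- **Section 8.3.12 (flow chart):** the row "Collecting adverse events" is marked for days 2-14 and again in the day-28 column.
- **Section 9.2.2:** "Serious Adverse Events (SAEs) will be reported from the first study-related procedure until discharge from the hospital", extended to study day 28 only for patients still in hospital then. The same paragraph adds "SAEs will be followed up for every patient on study day 28".
- **Section 9.4.3:** "SAEs need to be reported till end of study within the Netherlands, as defined in the protocol as treatment discontinuation for the last patient".
- **Section 12.9:** "The end of the study is defined as the last day of follow-up for the last patient (defined as discontinuation of treatment".

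Sections 9.5.1 and 10.3 have the SMC compare SAEs and thromboembolisms between the arms, with a significant excess on vitamin K2 leading to advice to halt the study.

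On anticoagulants, section 13.1 h states "Patients may not use VKAs during the study". Sections 4.3 and 7.5 admit former VKA users after a switch to heparin or LMWH. No section says when a VKA may be restarted.

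**The concern.** Treatment ends at discharge or on day 14, so for most patients the interval between leaving hospital and day 28 is the longest part of their follow-up. A thromboembolism or SAE in that interval is recordable under some sections and not under others. Two investigators, or one investigator with two patients, could handle the same event differently and both be following the protocol.

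Under 9.2.2 the window also depends on length of stay. If vitamin K2 changed the time to discharge, the arms would be observed for different lengths of time, and a comparison of event counts would mix the effect on events with the effect on observation time. The SMC uses exactly that comparison to advise on a halt, and with 10 patients per arm at its first review one or two events carry weight.

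**Working it through.** No figure in the protocol needs reproducing. The check sets the rules side by side and counts the days between them.

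**Inputs.** Study day 1 is the day of inclusion (8.3.2). Treatment runs to day 14 or discharge, whichever is earlier (5.1). The expected average stay is 6 days (section 3). The last follow-up is on day 28 (section 3, flow chart).

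**1. How each rule treats the same patient**

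| Patient | 8.3.3 / 9.2.1 (AEs) | 9.2.2 (SAE reporting) | 9.4.3 (SAE reporting) | Flow chart (AEs) |
|---|---|---|---|---|
| Early enrolee, discharged day 6 | closes day 6 | closes day 6 | open until the last patient in the trial stops treatment | ticked day 28 |
| Last enrolee, discharged day 6 | closes day 6 | closes day 6 | closes day 6 | ticked day 28 |
| Last enrolee, still admitted on day 28 | closes day 14 | closes day 28 | closes day 14 | ticked day 28 |

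In the first row 9.4.3 is longer than 9.2.2. In the third row it is shorter. Neither rule contains the other, so applying the stricter one does not resolve the conflict.

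**2. Size of the disputed interval**

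- Discharge on day 6: 28 - 6 = 22 days, which is 22/28 = 79% of the period to day 28.
- Full 14-day course ending at discharge: 28 - 14 = 14 days, or 50%.
- Still admitted on day 28: 0 days for SAEs under 9.2.2.

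The observed window under 9.2.2 therefore runs from about 6 days at the expected stay to 28 days for the sickest patients.

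**3. End of study.** Section 12.9 equates the last day of follow-up with treatment discontinuation, but section 3 and 9.2.2 schedule follow-up on day 28. For the last patient the study would formally end 14 to 22 days before that patient's own day-28 assessment.

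**4. Thromboembolisms.** The SMC compares these in addition to SAEs. No section gives them a window of their own. As adverse events of special attention (8.3.3) they fall under the rule that stops at discontinuation. A deep vein thrombosis treated without admission a week after discharge is then captured only if the flow-chart tick is followed.

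**5. VKA restart (minor).** The blood half-life of MK-7 is about 70 hours (section 6.1). With first-order decay the fraction left after d days is 0.5^(24d/70):

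- 7 days: 0.19
- 14 days: 0.036
- 22 days: 0.005

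Some MK-7 is therefore still present if a VKA is restarted soon after discharge. For the number concerned, the earlier cohort had 135 patients, and PIVKA-II was measured in the 122 not using VKAs (section 1.2, Figure 2). If all 13 others were VKA users, the share is 13/135 = 9.6%, and 0.096 x 40 = 3.9, so about 4 patients. This is an expected count. Under a binomial distribution with n = 40 and p = 13/135, the chance of more than 4 is 34% and the 95th percentile is 7.

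**The case against.** The strongest defence is that reporting an event and following it up are different activities. Read that way, 9.2.2 reports new SAEs to discharge and then checks on day 28 how known SAEs have resolved, and section 3 uses the same verb. The Summary limits the grade 3-4 endpoint to the treatment period, which agrees with 8.3.3 and 9.2.1. Section 9.4.3 could be taken as the sponsor's national reporting duty and not as a data-collection rule.

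Part of this stands. The day-28 sentences in section 3 and 9.2.2 do not by themselves contradict the discharge-based window, and an on-treatment window for the grade 3-4 endpoint is a legitimate choice. Two conflicts remain: 9.2.2 against 9.4.3, where a reporting duty cannot close on day 14 while the collection rule runs to day 28; and the flow-chart tick against 8.3.3 and 9.2.1. The defence also leaves the between-arm comparison dependent on length of stay.

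A reader might go further and infer that 13.1 h faces two rival end points, last treatment or day 28, and that VKAs should be barred to day 28. The documents do not support this. Section 9.4.3 concerns SAE reporting and 12.9 concerns notification of the authorities; neither mentions VKAs. No section calls day 28 the end of the study. Section 5.1 speaks of concomitant oral anticoagulants, which most naturally means use alongside study treatment. The clinical effect of residual MK-7 on a restarted VKA is not quantified anywhere in the protocol. A bar to day 28 could prolong heparin use, including in placebo patients who have no MK-7 to clear, and section 7.4 names bleeding as heparin's main risk.

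**Conclusion.** The event-window contradiction is real and should be corrected. About 22 of the 28 days are in dispute for a patient with the expected stay, and 14 for a patient who completes 14 days of treatment and then goes home. These figures assume discharge on the day treatment stops, inclusion close to admission, and no death before day 28. The flow-chart tick is read from a converted table, but the clash between 9.2.2 and 9.4.3 holds without it.

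The consequence is for safety capture and for the SMC's comparison. The desmosine and dp-ucMGP analyses and the sample size do not change. The direction of any bias is unknown, because it depends on whether vitamin K2 alters length of stay.

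The VKA point is minor: 13.1 h lacks a restart rule, and that is all the text supports. The figure of about 4 former VKA users is an expectation from another cohort. The true number could be higher by chance or through new anticoagulation indications during the study (section 5.2), or lower through the exclusion criteria.

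**What to change.** - **9.2.2, 9.4.3, 8.3.3 and the flow chart:** state one per-patient window. New SAEs and new thromboembolic or bleeding events are recorded from the first study procedure to study day 28 in every patient, whether discharged or not. Say that the day-28 follow-up covers new events as well as the outcome of known ones.
- **Grade 3-4 endpoint:** keep it on treatment. Add that limit to 8.1.2, where the Summary's qualifier is missing, and label the day-28 flow-chart tick as the SAE, thromboembolism and bleeding check.
- **12.9:** define the end of study as the last patient's study day 28.
- **8.4 and 8.6:** use study day 28 in place of 28 days after treatment or intervention.
- **9.5 and 9.5.1:** say whether the first SMC report is cut at the twentieth patient's day 14 or at completed follow-up. If day 14 is kept, the report should note which patients have not yet reached day 28.
- **13.1 h:** add one sentence noting the half-life of about 70 hours and advising INR monitoring when a VKA is restarted after study treatment, in both arms so that blinding holds.

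The cost is modest but not zero. Under 8.6 the day-28 contact may be only a file check or a call to establish vital status. It would have to ask about these events, with matching eCRF fields, for 40 patients. Moving the end of study to the last patient's day 28 postpones formal closure by 14 to 22 days.
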